S1B : English version

**FOLFOX4 versus sequential dose-dense FOLFOX7 followed by FOLFIRI in patients with resectable metastatic colorectal cancer. A GERCOR randomized phase III study (MIROX).**

Sponsor: GERCOR

Coordinator Principal: [name]

[name], Service d’Oncologie Médicale, Centre Hospitalo-Universitaire, [name], [contact], [contact], Email: [[contact]](mailto:[contact])

The United States National Health Institute registry identifier: NCT00268398.

**TRIAL DESCRIPTION**: Open-label, randomized phase III trial.

**PURPOSE**: To determine whether a sequential chemotherapy of 5-fluorouracil (5-FU)/leucovorin (LV) with dose-dense oxaliplatin (FOLFOX7) and irinotecan-based 5-FU/LV (FOLFIRI) is superior to FOLFOX4 in patients with resectable metastases from colorectal cancer (CRC).

**OBJECTIVES**:

***Primary***

• 2-year disease-free survival (DFS) rate.

***Secondary***

• Overall survival (OS).

• Toxicity (according to the National Cancer Institute Common Toxicity Criteria, version 2.0).

• Health-related quality of life (HRQoL).

• Objective response rate (ORR).

• In case of perioperative chemotherapy:

- Tumor response according to the RECIST 1.0
- Resection type (R0 vs. R1 vs. R2).

• Postoperative complication rate.

• Transfusing rate in patients having metastasis surgery.

• Pharmacogenetics.

**TREATMENT PLAN:**

Patients will be randomized to 1 of 2 treatment arms:

•Arm I (12 cycles of FOLFOX 4): Patients will receive FOLFOX 4 chemotherapy comprising leucovorin 200 mg/m2 by infusion over 2 hours on days 1- 2, oxaliplatin 85 mg/m2 by infusion over 2 hours on day 1, fluorouracil 400 mg/m2 over 15 min on days 1- 2, then fluorouracil 1200 mg/m2 over 46 hours. Treatment will repeat every 2 weeks for 12 courses in the absence of disease progression or unacceptable toxicity.

•Arm II (6 cycles of FOLFOX 7 and FOLFIRI): Patients will receive 6 cycles FOLFOX 7 combination chemotherapy comprising high-dose oxaliplatin 130mg/m2 infusion on day 1 in combination with leucovorin 200 mg/m2 by infusion over 2 hours followed by fluorouracil 2400 mg/m2 by continuous infusion over 46 hours followed by 6 cycles of FOLFIRI consisted of irinotecan 180 mg/m2 by 30-90 min infusion in combination with leucovorin 200 mg/m2, fluorouracil 400 mg/m2 over 15 min on day 1, followed by fluorouracil 2400 mg/m2 over 46 hours. Treatment will repeat every 2 weeks for 6 courses in the absence of disease progression or unacceptable toxicity.

Simple or complex surgical procedures will be authorized, provided resection will be complete or considered to be initially feasible in case of preoperative chemotherapy. Patients who will undergo R2 (residual tumor) resection will be taken off the study. In patients operated before the entry into the study, a R0 resection will be required.

**DOSE MODIFICATION**

Toxicity will be evaluated before each cycle and following dose modification will be used for subsequent cycles:

***FOLFOX4:***

If neurological symptoms will occur, the following oxaliplatin dosage adjustment will be recommended, based on the duration and severity:

- Paraesthesia associated with pain or functional impairment

- non persistent (≤7 days) - oxaliplatin won't be modified,
- persistent >7 days and <14 days,

- if neurologic examination normal – oxaliplatin dose will be reduced from 85 to 75 mg/m2,

- if neurologic examination abnormal - the cycle of therapy will be omitted with resumption of therapy at the scheduled next cycle, with oxaliplatin dose reduction to 75 mg/m2,

- persisted between cycles - therapy will be interrupted until improvement and resumed at 75 mg/m2 oxaliplatin.

- Neutropenia

grade 3/4 (NCI/CTC) – bolus 5-FU dose will be reduced from 400 to 300 mg/m2 and continuous 5-FU dose will be reduced from 600 to 500 mg/m2/day, oxaliplatin dose will be reduced from 85 to 75 mg/m2.

- Nausea and/or vomiting despite premedication -

grade 4 (NCI/CTC) - oxaliplatin dose will be reduced from 85 to 75 mg/m2 with antiemetics adjustment; if intolerable toxicity, patient will leave the study after agreement between the principal investigator and physician.

- Diarrhoea or mucositis

grade 3 (NCI/CTC) - bolus 5-FU dose will be reduced from 400 to 300 mg/m2 and continuous 5-FU dose will be reduced from 600 to 500 mg/m2/day,

grade 4 (NCI/CTC) - bolus 5-FU dose will be reduced from 400 to 300 mg/m2 and continuous 5-FU dose will be reducded from 600 to 500 mg/m2/day,oxaliplatin dose will be reduced from 85 to 75 mg/m2.

- Central neurological and cardiac toxicity (especially angina pectoris) - treatment discontinuation.

- Cutaneous toxicity

grade 3/4 (NCI/CTC) - bolus 5-FU dose will be reduced from 400 to 300 mg/m2 and continuous 5-FU dose will be reduced from 600 to 500 mg/m2/day.

- Other toxicity - bolus 5-FU dose will be reduced from 400 to 300 mg/m2 and continuous 5-FU dose will be reduced from 600 to 500 mg/m2/day, oxaliplatin dose will be reduced from 85 to 75 mg/m2.

- Persistent thrombocytopenia >75000/mm3 - treatment will be continued after decision of the principal investigator.

- If grade 3/4 toxicities persist, following cycles will be carried at the lower level, except in cases of uncomplicated neutropenia (<7 days, recovery after 15 days).

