***FOLFOX7:***

If neurological symptoms will occur, the following oxaliplatin dosage adjustment will be recommended, based on the duration and severity:

- Paraesthesia associated with pain or functional impairment:

- non persistent (≤7 days) - oxaliplatin dose won’t be modified,
- persistent >7 days and <14 days : oxaliplatin dose will be reduced from 130 to 100 mg/m2,
- persisted between cycles – oxaliplatin will be interrupted. The patient will subsequently receive FOLFIRI for a total (FOLFOX + FOLFIRI) of 12 cycles.

- Neutropenia

grade 3/4 (NCI/CTC) - 5-FU: 2000mg/m2 after recovery, oxaliplatin: 100 mg/m2after recovery.

- Thrombopenia

grade 3/4 (NCI/CTC) – 5-FU: 2000mg/m2, oxaliplatin: 100 mg/m2 after recovery.

- Mucositis

grade 3/4 (NCI/CTC) – 5-FU: 2000mg/m2, oxaliplatin: 100 mg/m2 after recovery.

- Diarrhoea -

grade 3/4 (NCI/CTC) - 5-FU 2000mg/m2.

Cutaneous toxicity

grade 3/4 (NCI/CTC) - 5-FU 2000mg/m2.

- Central neurological and cardiac toxicity (especially angina pectoris) - treatment discontinuation.

- Persistent thrombocytopenia >75000/mm3- treatment will be continued after decision of the principal investigators.

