***FOLFIRI:***

- Neutropenia

grade 2 (NCI/CTC) - 5-FU: 100% after recovery, irinotecan 150 mg/m2,

grade 3/4 (NCI/CTC) – 5-FU: 2000mg/m² after recovery, irinotecan 150 mg/m2.

- Thrombopenia

grade 2 (NCI/CTC) – 5-FU: 100% after recovery, irinotecan 150 mg/m2,

grade 3 (NCI/CTC) – 5-FU: 2000mg/m² after recovery, irinotecan 150 mg/m2,

grade 4 (NCI/CTC) – patient will leave the study.

- Mucositis

grade 3/4 (NCI/CTC) – 5-FU: 2000mg/m2, irinotecan 150 mg/m2.

- Diarrhoea

grade 2 (NCI/CTC) - 1st occurrence – 5-FU dose will be lowered and continued at 2000mg/m2, 2nd occurrence irinotecan 150 mg/m2,

grade 3/4 (NCI/CTC) – 5-FU: 2000mg/m2, irinotecan 150 mg/m2.

- Cutaneous toxicity

grade 3 (NCI/CTC) - 5-FU 2000mg/m2,

grade 4 (NCI/CTC) - patient will leave the study.

- Angina pectoris - patient will leave the study.

- Persistent thrombocytopenia >75000/mm3- treatment will be continued after decision of the principal investigators.

- In case of persistent grade 3/4 toxicities, following cycles will be carried at the lower level, except in cases of uncomplicated neutropenia <7 days, and recovery after 15 days.

- In case of persistent diarrhoea grade >2 or severe neutropenia (grade 4 > 7 days or febrile neutropenia) despite decrease in irinotecan to 150 mg/m², the treatment will be discontinued and the patient will leave the study.

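### The FOLFOX4 rule for 'Other toxicity' orders a three-part dose cut without saying what grade triggers it; it is the only FOLFOX4 reduction rule with no threshold

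*Protocol*

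**What the plan says.** The Dose Modification section of the Protocol has toxicity assessed before every cycle and states that the "following dose modification will be used for subsequent cycles". It sets no minimum grade that would apply to all the lists below it.

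In the FOLFOX4 list, the rule for toxicities not named elsewhere begins "Other toxicity - bolus 5-FU dose will be reduced from 400 to 300 mg/m2 and continuous 5-FU dose will be reduced from". The infused dose goes down to 500 mg/m2/day from a full 600, and oxaliplatin is lowered from 85 to 75 mg/m2. No grade, duration or clinical criterion is attached.

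The neighbouring rules do carry one. The neutropenia rule begins with its trigger: "grade 3/4 (NCI/CTC) – bolus 5-FU dose will be reduced from 400 to 300 mg/m2 and continuous 5-FU dose will be reduced from". The reduced doses there are the same as in the residual rule, with oxaliplatin again at 75 mg/m2. For nausea or vomiting: "grade 4 (NCI/CTC) - oxaliplatin dose will be reduced from 85 to 75 mg/m2 with antiemetics adjustment". For paraesthesia with pain or functional impairment lasting more than 7 and less than 14 days: "if neurologic examination normal – oxaliplatin dose will be reduced from 85 to 75 mg/m2". The FOLFOX4 list ends with a line on persistence: "If grade 3/4 toxicities persist, following cycles will be carried at the lower level", with an exception for uncomplicated neutropenia.

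**The concern.** The line is a directive, not a silence: it says the doses will be reduced. The softer word 'recommended' in the FOLFOX4 list introduces only the oxaliplatin adjustment for neurological symptoms. A site that follows the text would cut both 5-FU components and oxaliplatin after a grade 1 unlisted event. A site that infers grade 3/4 from the surrounding rules would leave full doses in place for the same event. Control-arm dosing would then depend on how each site completes an incomplete line, in an open-label trial whose purpose is to show superiority over that control.

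The gap also reaches a toxicity that the Protocol names elsewhere. FOLFOX4 has no graded reduction for thrombopenia. It has only a line on continuing treatment, by decision of the principal investigator, in persistent thrombocytopenia above 75000/mm3. A first occurrence of thrombopenia on FOLFOX4 therefore plausibly falls under the ungraded residual line.

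**Working it through.** No statistical figure is involved. The check is a count of the FOLFOX4 rules and simple dose arithmetic.

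**Step 1. Every FOLFOX4 rule that lowers a dose, with its trigger.**

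| # | Toxicity | Trigger | What is reduced |
|---|---|---|---|
| 1 | Paraesthesia with pain or functional impairment | >7 and <14 days, normal examination | Oxaliplatin |
| 2 | Same | >7 and <14 days, abnormal examination | Cycle omitted, then oxaliplatin |
| 3 | Same | Persists between cycles | Interruption, then oxaliplatin |
| 4 | Neutropenia | Grade 3/4 | Bolus 5-FU, infused 5-FU, oxaliplatin |
| 5 | Nausea/vomiting despite premedication | Grade 4 | Oxaliplatin |
| 6 | Diarrhoea or mucositis | Grade 3 | Bolus and infused 5-FU |
| 7 | Diarrhoea or mucositis | Grade 4 | Bolus 5-FU, infused 5-FU, oxaliplatin |
| 8 | Cutaneous | Grade 3/4 | Bolus and infused 5-FU |
| 9 | Other | **None stated** | Bolus 5-FU, infused 5-FU, oxaliplatin |

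Rules with a threshold: 3 + 1 + 1 + 2 + 1 = 8. Rules without: 1. The central neurological and cardiac line also has no grade, but it orders discontinuation, not a reduction. The persistent thrombocytopenia line concerns continuing treatment.

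**Step 2. Size of the cut per affected cycle.** Full and reduced doses are from the FOLFOX4 list. The infusion of 600 mg/m2/day over 2 days is 1200 mg/m2, which agrees with the Treatment Plan.

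- Bolus 5-FU: (400 − 300)/400 = 25.0%.
- Infused 5-FU: (600 − 500)/600 = 16.7%.
- Total 5-FU: 2 × (400 + 600) = 2000 mg/m2 falls to 2 × (300 + 500) = 1600 mg/m2; 400/2000 = 20.0%.
- Oxaliplatin: (85 − 75)/85 = 11.8%.

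**Step 3. Comparison with graded rules.** The ungraded line orders exactly the cut set for grade 3/4 neutropenia (rule 4) and grade 4 diarrhoea or mucositis (rule 7). It goes further than the rule for grade 3 diarrhoea or mucositis (rule 6), which leaves oxaliplatin at 85 mg/m2. Read literally, a grade 1 unlisted event is treated more severely than grade 3 diarrhoea.

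**Step 4. Can the missing grade be read from the context?** Only as a likelihood. All five rules with an NCI-CTC grade (4 to 8) start at grade 3 or 4, and the persistence line speaks of grade 3/4. But the same three-part cut starts at grade 3 for neutropenia and only at grade 4 for diarrhoea or mucositis, so two analogies are available. The persistence line governs later cycles and supplies no initial trigger.

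**The case against.** The strongest reply is that this is a dropped label and nobody would follow the literal reading. Every graded FOLFOX4 reduction starts at grade 3 or 4, and a three-part cut for a mild event would be out of line with the rest of the list. The percentages above are those of the ordinary FOLFOX4 reduction step; they describe what the line orders, not how much harm the omission does. The document is also headed as an English version, and whether a source-language text carries the grade cannot be checked. All of this stands. It makes a grade 3/4 intent likely and keeps the point minor, but it does not put a grade in the line.

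A reader might go further and infer an imbalance between the arms: the control arm has a catch-all reduction, and neither the FOLFOX7 nor the FOLFIRI list has an initial rule for unlisted toxicities. The Protocol does not support treating that as a defect. The arms use different drugs, so regimen-specific lists are to be expected and need no catch-all. The comparison also runs the other way. FOLFOX7 has an explicit thrombopenia reduction, "grade 3/4 (NCI/CTC) – 5-FU: 2000mg/m2, oxaliplatin: 100 mg/m2 after recovery", and FOLFIRI reduces at grade 2 for neutropenia, thrombopenia and diarrhoea, which is lower than any graded FOLFOX4 trigger. FOLFIRI also has a general line, "In case of persistent grade 3/4 toxicities, following cycles will be carried at the lower level", that could reach unlisted events.

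**Conclusion.** The point holds as a drafting omission in one treatment instruction. One of nine FOLFOX4 reduction rules has no threshold, and as written it lowers total 5-FU by 20.0% and oxaliplatin by 11.8% per affected cycle for any unlisted toxicity, however mild. Those figures assume the line is followed literally. If sites read it as grade 3/4, which is probably what was meant, nothing changes in practice.

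A reader might also infer that the control arm was under-dosed and the comparison tilted towards FOLFOX7-FOLFIRI. The Protocol gives no frequency of unlisted events and no record of how sites read the line. The number of cycles affected, any effect on disease-free survival and the direction of any net bias therefore cannot be determined, and none is claimed. Severity is minor. Confidence is high that the trigger is absent; the practical consequence is unknown.

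**What to change.** In the FOLFOX4 list, change the label of the residual line to 'Other toxicity grade 3/4 (NCI/CTC)'. The clinical team should confirm the grade, since grade 4 alone would also be defensible by analogy with diarrhoea and mucositis. With grade 3/4, thrombopenia falling under this line would have the same trigger as in FOLFOX7. Send sites a short memo.

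Leave the FOLFOX7 and FOLFIRI lists unchanged. Adding a matching catch-all to FOLFIRI would do harm. Patients whose paraesthesia persists between FOLFOX7 cycles are moved to FOLFIRI, whose list has no paraesthesia rule, so the new line could cut 5-FU and irinotecan for residual oxaliplatin neuropathy. The FOLFIRI list also names only angina pectoris, so a catch-all would prescribe reduced-dose continuation for central neurological or other cardiac toxicity, where the FOLFOX4 and FOLFOX7 lists discontinue.

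The cost is one grade label and one memo, with no added patients, visits or procedures.

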***FOLFOX7:***

If neurological symptoms will occur, the following oxaliplatin dosage adjustment will be recommended, based on the duration and severity:

- Paraesthesia associated with pain or functional impairment:

- non persistent (≤7 days) - oxaliplatin dose won’t be modified,
- persistent >7 days and <14 days : oxaliplatin dose will be reduced from 130 to 100 mg/m2,
- persisted between cycles – oxaliplatin will be interrupted. The patient will subsequently receive FOLFIRI for a total (FOLFOX + FOLFIRI) of 12 cycles.

- Neutropenia

grade 3/4 (NCI/CTC) - 5-FU: 2000mg/m2 after recovery, oxaliplatin: 100 mg/m2after recovery.

- Thrombopenia

grade 3/4 (NCI/CTC) – 5-FU: 2000mg/m2, oxaliplatin: 100 mg/m2 after recovery.

- Mucositis

grade 3/4 (NCI/CTC) – 5-FU: 2000mg/m2, oxaliplatin: 100 mg/m2 after recovery.

- Diarrhoea -

grade 3/4 (NCI/CTC) - 5-FU 2000mg/m2.

Cutaneous toxicity

grade 3/4 (NCI/CTC) - 5-FU 2000mg/m2.

- Central neurological and cardiac toxicity (especially angina pectoris) - treatment discontinuation.

- Persistent thrombocytopenia >75000/mm3- treatment will be continued after decision of the principal investigators.

***FOLFIRI:***

- Neutropenia

grade 2 (NCI/CTC) - 5-FU: 100% after recovery, irinotecan 150 mg/m2,

grade 3/4 (NCI/CTC) – 5-FU: 2000mg/m² after recovery, irinotecan 150 mg/m2.

- Thrombopenia

grade 2 (NCI/CTC) – 5-FU: 100% after recovery, irinotecan 150 mg/m2,

grade 3 (NCI/CTC) – 5-FU: 2000mg/m² after recovery, irinotecan 150 mg/m2,

grade 4 (NCI/CTC) – patient will leave the study.

- Mucositis

grade 3/4 (NCI/CTC) – 5-FU: 2000mg/m2, irinotecan 150 mg/m2.

- Diarrhoea

grade 2 (NCI/CTC) - 1st occurrence – 5-FU dose will be lowered and continued at 2000mg/m2, 2nd occurrence irinotecan 150 mg/m2,

grade 3/4 (NCI/CTC) – 5-FU: 2000mg/m2, irinotecan 150 mg/m2.

- Cutaneous toxicity

grade 3 (NCI/CTC) - 5-FU 2000mg/m2,

grade 4 (NCI/CTC) - patient will leave the study.

- Angina pectoris - patient will leave the study.

- Persistent thrombocytopenia >75000/mm3- treatment will be continued after decision of the principal investigators.

- In case of persistent grade 3/4 toxicities, following cycles will be carried at the lower level, except in cases of uncomplicated neutropenia <7 days, and recovery after 15 days.

- In case of persistent diarrhoea grade >2 or severe neutropenia (grade 4 > 7 days or febrile neutropenia) despite decrease in irinotecan to 150 mg/m², the treatment will be discontinued and the patient will leave the study.

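### Among cardiac and central neurological toxicities, the FOLFIRI dose rules mandate a stop only for angina, whereas both FOLFOX lists stop treatment for the whole category

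*Protocol*

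**What the plan says.** The Dose Modification section has a separate list for each regimen. The FOLFOX4 and FOLFOX7 lists carry the same line: "Central neurological and cardiac toxicity (especially angina pectoris) - treatment discontinuation". Angina is named there as an example within a class. The corresponding entry in the FOLFIRI list is "Angina pectoris - patient will leave the study". Here angina is the whole rule, and the action is worded as leaving the study rather than stopping treatment.

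Two general provisions could also apply during FOLFIRI:

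- The Treatment Plan for Arm II states: "Treatment will repeat every 2 weeks for 6 courses in the absence of disease progression or unacceptable toxicity". Unacceptable toxicity is not defined.
- The FOLFIRI list states: "In case of persistent grade 3/4 toxicities, following cycles will be carried at the lower level, except in cases of uncomplicated neutropenia". The exception is limited to short, recovering neutropenia.

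**The concern.** Sites act on these lists cycle by cycle. An Arm II patient is under the broad stop rule while on FOLFOX7 and under an angina-only rule after the switch to FOLFIRI. The Treatment Plan shows that FOLFIRI also contains fluorouracil, both as bolus and as infusion ("fluorouracil 400 mg/m2 over 15 min on day 1, followed by fluorouracil 2400 mg/m2 over 46 hours"), so the change of regimen does not remove a component common to all three. The protocol does not explain why the stop should narrow.

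What is at stake is consistent handling of a potentially serious event. A stop that is explicit and mandatory on two regimens becomes a matter of judgement on the third, and two sites could treat the same event differently. No statistical quantity depends on it.

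**Working it through.** The plan states no figure to reproduce, so the check is a comparison of the three lists and of the rules that remain for the omitted events.

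**Step 1: the three lists side by side**

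| Event | FOLFOX4 list | FOLFOX7 list | FOLFIRI list |
|---|---|---|---|
| Angina | stop treatment | stop treatment | leave the study |
| Other cardiac toxicity | stop treatment | stop treatment | no entry |
| Central neurological toxicity | stop treatment | stop treatment | no entry |
| Catch-all line for other toxicities | yes (dose reduction) | none | none |
| General rule for persistent grade 3/4 toxicity | yes (lower level) | none | yes (lower level) |

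**Step 2: the other FOLFIRI stops.** The list also removes patients for grade 4 thrombopenia ("grade 4 (NCI/CTC) – patient will leave the study"), for grade 4 cutaneous toxicity, and for persistent diarrhoea above grade 2 or severe neutropenia despite irinotecan at 150 mg/m2. None of these reaches a cardiac or central neurological event. The word *only* in the heading therefore applies within that category and not to the list as a whole.

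**Step 3: what governs the two empty cells.** The persistent grade 3/4 rule presupposes a lower dose level, and the FOLFIRI list sets none for these events. It neither mandates a stop nor gives a workable reduction. That leaves the Treatment Plan's unacceptable-toxicity condition. It applies to every further cycle, but the decision is the investigator's.

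**Step 4: whether the change of drugs explains the narrower rule.** FOLFIRI contains irinotecan, leucovorin and fluorouracil, and no oxaliplatin.

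- *Cardiac events.* The FOLFIRI list keeps an angina stop in a regimen without oxaliplatin, so the authors did not regard cardiac stops as an oxaliplatin matter alone. Dropping the other cardiac events is then hard to explain.
- *Central neurological events.* The wording appears in the two regimens with oxaliplatin and is absent from the one without. That pattern fits an omission, and it also fits a deliberate choice. The protocol does not say which drug motivates the line.

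**Step 5: who is exposed.** The gap can arise only in Arm II (142 planned patients) and only for events first seen on FOLFIRI, because the FOLFOX7 list already stops patients with an earlier event. FOLFIRI is 6 of the 12 planned cycles. It is more for patients moved to it early because paraesthesia persists between FOLFOX7 cycles. The protocol gives no event frequency, so no expected count can be computed.

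**The case against.** The strongest case on the other side is that the lists are regimen-specific and differ in many lines, so one difference does not prove an error. FOLFIRI is not the laxer list overall. It removes patients at grade 4 cutaneous toxicity where both FOLFOX lists reduce the dose, and at grade 4 thrombopenia where FOLFOX7 reduces. It keeps angina, the one event the FOLFOX lists single out. The unacceptable-toxicity condition is a real backstop, and most investigators would probably stop anyway. All of this stands, and it limits the point to a minor one. It does not supply a reason for dropping the non-anginal cardiac events, and it does not turn a judgement into a rule.

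Three stronger readings are tempting, and the protocol supports none of them:

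- *FOLFIRI directs reduced-dose continuation after such an event.* The lower-level rule does not exclude these events, so a reader might infer this. But it concerns persistent grade 3/4 toxicity, no reduced level is set for these events, and the unacceptable-toxicity condition still applies.
- *The rule narrows just as fluorouracil exposure, and hence risk, rises.* Planned fluorouracil per cycle is 400 + 2400 = 2800 mg/m2 in FOLFIRI against 2400 mg/m2 in FOLFOX7 ("followed by fluorouracil 2400 mg/m2 by continuous infusion over 46 hours"). The protocol gives no relation between dose and these toxicities, and it does not name fluorouracil as the reason for the stop. The difference is not a measure of harm.
- *Leaving the study for angina ends disease-free survival follow-up and biases the comparison.* The protocol does not say that it ends follow-up, and its modified intent-to-treat population is every randomised patient given at least one dose, which includes anyone who has reached FOLFIRI.

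**Conclusion.** The inconsistency is real and can be verified from the text. Within the cardiac and central neurological category, FOLFIRI has a mandatory stop for angina alone, while FOLFOX4 and FOLFOX7 stop for the entire category. For anything else in that category first arising on FOLFIRI, stopping depends on an undefined general condition.

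Confidence is high on the textual difference and lower on its consequence. The cardiac half rests on the FOLFIRI list's own angina stop in a regimen without oxaliplatin. The central neurological half rests on the assumption that the stop is not specific to oxaliplatin, which the protocol neither confirms nor denies. The number of patients affected is unknown and probably small. The point is a minor patient-safety harmonisation. Sample size, endpoint and tests are untouched.

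**What to change.** In the FOLFIRI list, replace the angina line with the one used in the FOLFOX4 and FOLFOX7 lists: "Central neurological and cardiac toxicity (especially angina pectoris) - treatment discontinuation". The action should be identical in all three lists. Keeping a separate leave-the-study instruction for angina would preserve part of the inconsistency.

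No explicit carve-out from the lower-level rule is needed. The FOLFOX4 list already has such a rule beside its specific stop line, and the specific line governs. If the narrower FOLFIRI rule was deliberate, one sentence saying so and giving the reason would settle the point instead.

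The cost is one replaced line and a notice to sites, with no extra data or patients.

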**ENDPOINTS EVALUATION**

• DFS defined as the interval between randomization and first evidence of relapse (local, regional, metastases or second CRC), or death from any cause.

• OS defined as the interval between randomization and patient death from any cause.

• Toxicity assessed according to the National Cancer Institute Common Toxicity Criteria (NCI-CTC) criteria, version 2.0.

• Tumor response (complete response, partial response, stable disease, progressive disease), ORR and disease control rate assessed according to the RECIST 1.0 criteria.

• HRQoL assessed using the European Organization for Research and Treatment of Cancer (EORTC) self-administered Quality of Life Questionnaire (QLQ-C30) at baseline and at 8, 16 and 24 weeks.

• Time until definitive deterioration (TUDD) used for longitudinal analyses defined as the interval between randomization and the first observation of a definitive deterioration of QLQ-C30 score, the later including 5 points decrease in QoL score compared to the QoL score at baseline, no improvement in QoL score ≥5 points as compared with baseline or patient drop-out after ≥5 points decrease resulting in missing data or death.

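### Study-exit wording differs by regimen (four toxicity rules under FOLFIRI, one under FOLFOX4, none under FOLFOX7), and the protocol never says that these patients stay in DFS and OS follow-up

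*Protocol*

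**What the plan says.** The exit rules stand in the protocol's Dose Modification and Treatment Plan sections.

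- **FOLFIRI (Arm II only), four rules.** Grade 4 thrombopenia and grade 4 cutaneous toxicity have the same consequence: "grade 4 (NCI/CTC) – patient will leave the study". For angina: "Angina pectoris - patient will leave the study". For persistent diarrhoea or severe neutropenia despite the reduced irinotecan dose: "the treatment will be discontinued and the patient will leave the study".
- **FOLFOX4 (Arm I), one rule.** It concerns nausea and vomiting and is discretionary: "if intolerable toxicity, patient will leave the study after agreement between the principal investigator and physician". For cardiac events, including angina, the rule is "Central neurological and cardiac toxicity (especially angina pectoris) - treatment discontinuation".
- **FOLFOX7 (Arm II, first six cycles), none.** The cardiac rule has the same wording as under FOLFOX4.
- **Treatment Plan, both arms.** "Patients who will undergo R2 (residual tumor) resection will be taken off the study". The power section lists R2 resections among the causes of its 20% drop-out.

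On endpoints, the protocol has "DFS defined as the interval between randomization and first evidence of relapse" or death from any cause, and "OS defined as the interval between randomization and patient death from any cause". Treatment Evaluation sets examinations every 3 months for 2 years and every 6 months after that. The efficacy analysis takes all randomized patients with at least one dose of chemotherapy. None of these sections mentions patients who have left the study.

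**The concern.** DFS and OS run from randomization to relapse or death, and the analysis set keeps every treated patient. Both need follow-up after protocol treatment stops. A site that applies the FOLFIRI rules literally would stop collecting exactly those data, and four of the five toxicity exit rules apply only in the experimental arm.

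Two features make the wording hard to dismiss. One FOLFIRI rule names stopping treatment and leaving the study as two consequences in one sentence. And the same event, angina, has a different consequence under FOLFIRI from that under the two FOLFOX regimens.

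If leavers were censored at exit and their later risk differed from that of patients who stayed, the assumption of non-informative censoring behind Kaplan-Meier and the log-rank test would fail, and more so in one arm. An analysis plan cannot recover follow-up that was never collected.

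**Working it through.** **1. The plan's own figure.** Freedman's formula with HR 0.66, two-sided 5% and 80% power gives ((1 + 0.66)/(1 − 0.66))² × (1.960 + 0.842)² = 187.1, rounded up to 188. The stated 188 events reproduce.

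**2. Count of toxicity exit rules.**

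| Regimen | Arm | Study-exit rules | Consequence of angina |
|---|---|---|---|
| FOLFOX4 | I | 1 | treatment stops |
| FOLFOX7 | II | 0 | treatment stops |
| FOLFIRI | II | 4 | patient leaves the study |

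**3. Possible bias in Arm II 2-year DFS.**

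From the protocol: 2-year DFS of 45% in Arm II and 30% in Arm I. Assumed, because the documents do not give them: exponential DFS; a share q of Arm II patients still event-free at month 5 leaves and is censored then; the later hazard of leavers is m times that of patients who stay.

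- Hazard of patients who stay: λ = −ln(0.45)/24 = 0.03327 per month.
- Event-free at month 5: exp(−5λ) = 0.8467.
- Survival from month 5 to 24 for patients who stay: c = exp(−19λ) = 0.5314.
- The Kaplan-Meier estimate with leavers censored is 0.8467 × 0.5314 = 0.450.
- The value with everyone followed is 0.8467 × [(1 − q)c + q·c^m].
- The error is therefore 0.8467 × q × (c − c^m).

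| q | m | c^m | DFS, all followed | Error in Kaplan-Meier, points |
|---|---|---|---|---|
| 2% | 1.5 | 0.3874 | 0.448 | +0.24 |
| 5% | 1.5 | 0.3874 | 0.444 | +0.6 |
| 10% | 1.5 | 0.3874 | 0.438 | +1.2 |
| 10% | 2 | 0.2824 | 0.429 | +2.1 |
| 10% | 1 | 0.5314 | 0.450 | 0 |
| 10% | 0.7 | 0.6424 | 0.459 | −0.9 |

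**4. Possible effect on the test.** This uses a similar model with exit at month 4.5 in Arm II only, no true difference (30% in both arms) and 188 events. With 10% leaving and m from 1.5 to 3, the apparent HR is 0.968 to 0.927 and the two-sided type I error 5.6% to 8.1%. With 2% leaving it is 5.0% to 5.1%. With m = 1 it stays at 5%.

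**5. Events and power.** Accrual over 36 months and 24 months of follow-up are read as censoring uniform on 24 to 60 months. The probability of an observed event is 1 − (exp(−24λ) − exp(−60λ))/(36λ), which is 0.738 in Arm II and, with λ = −ln(0.30)/24 = 0.05017, 0.861 in Arm I.

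- Expected events with all 284 patients followed: 142 × (0.738 + 0.861) ≈ 227. With 248 patients: about 198.
- Assume 10% leave in Arm II and 2% in Arm I at month 5, with m = 1. Arm II loses 142 × 0.10 × (0.738 − 0.153) = 8.3 events. Arm I loses 142 × 0.02 × (0.861 − 0.222) = 1.8. The total is about 10.
- Even if all 10 came straight off 188, power at HR 0.66 by Schoenfeld's approximation would fall from Φ(√(188/4) × 0.4155 − 1.96) = 81.3% to Φ(√(178/4) × 0.4155 − 1.96) = 79.2%.

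**The case against.** The strongest reply is that leaving the study here may mean leaving study treatment. The phrase stands under Dose Modification, which governs treatment. The sections on endpoints, examinations and analysis contain no toxicity exit, and the drop-out causes in the power section do not include toxicity. The English text is loose in other places, so the two phrases for angina could be interchangeable. This stands as a possible reading. It does not settle the matter: the protocol never says so, one sentence names both consequences, and R2 patients taken off study are counted as drop-out, which points the other way.

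A reader might go further and infer that these rules do create informative, arm-dependent censoring that favours the experimental arm. The documents do not support that. No section says that leavers are censored at exit, nothing links leaving to prognosis, and no exit rate or later hazard is given. The direction reverses if leavers do better. Rule counts are also not patient counts: three of the four FOLFIRI triggers are two grade 4 toxicities and angina, and the fourth applies only when toxicity persists after a dose reduction.

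A reader might also set about 10 lost events against the required 188 and see a shortfall. Under the same model the loss comes off roughly 227 expected events with all 284 followed, so it does not by itself take the trial below 188. That 227 does allow for no other drop-out.

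**Conclusion.** The point holds as a gap and an inconsistency in the protocol's conduct rules. Exit wording differs by regimen and for the same event, R2 resection is a further off-study route, and continued follow-up is nowhere stated although the endpoints and analysis set depend on it. The uneven loss by arm follows from a literal reading.

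Bias is possible but not shown. Under assumed exit of 2-10% in Arm II at month 5, the error in its 2-year DFS runs from about +0.2 to +2.1 points at 1.5-2 times the later hazard, is nil at equal hazard, and is about −0.9 points at 0.7 times the hazard with 10% leaving. Against the planned 15-point difference these are modest figures, and the power cost is small. The change is worth making because it is cheap and the follow-up cannot be recovered later.

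**What to change.** Reconcile the wording on leaving the study, being taken off study and discontinuing treatment in the Treatment Plan and in the FOLFOX4, FOLFOX7 and FOLFIRI dose sections, with the same follow-up wording for all three regimens. Then add one statement: patients who stop protocol treatment for toxicity or after R2 resection stay in DFS and OS follow-up on the Treatment Evaluation schedule and are analysed in their randomized arm. Including R2 resection matters, because otherwise an explicit off-study route remains open in both arms.

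The rules on when treatment stops are not changed, and no view is taken on them. The cost is a wording amendment and continued follow-up of a few patients on existing visits.
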